### Methods for additional analyses

The hybrid control will use multivariate logistic regression and odds ratio and 95% confidence interval estimation. Clinically significant variables from the univariate analysis will be included in the multivariate model. Goodness-of-fit will be evaluated through the Hosmer–Lemeshow test. Statistical analysis will be performed by using SPSS 22.0. A two-tailed significance level of 0.05 will be used for all tests. *P* < 0.05 will indicate statistical significance.

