## Methods: participants, interventions, and outcomes

### Study setting

The study will be completed at three research centres.

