### Sample size

This study is a superiority trial. Our pretest showed that the average wound healing times of the graft and no-graft groups were approximately 15 and 25 days, respectively. We assume that no difference in efficacy exists among the three centres. Assuming a two-sided significance level of 0. 05 and power of 80% (*α* = 0. 05, *β* = 0. 2), the sample size is calculated as 47 (fixed model as $$n_{1} = n_{2} = \frac{{\sigma^{2} \left( {{\text{t}}_{\alpha } + t_{\beta } } \right)^{2} }}{{\delta^{2} }}$$) [11]. Considering a loss to follow-up of 10%, the sample size for each group is 52 cases, and the total is 104 cases.

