### Recruitment

This RCT, in which assessors and patients are blinded, will be conducted at three research centres. The subjects in this study will be recruited from outpatient and inpatient wards by placing advertisements on social media platforms and distributing posters with details of the study and contact information in public areas of hospitals.

Patients who meet the inclusion criteria will be invited to participate in the study and provided with the details of the RCT protocol. All patients will be required to sign an informed consent form and provide complete information. The patients will be randomised (1:1) to the test and control groups. None of the patients will know about their assigned group to keep the trial blind. Then, their baseline characteristics will be assessed, and a database record will be obtained by the same colorectal surgeon. All patients will be treated with surgery and followed up on the 3rd day, 7th day, 14th day, 21st day, 28th day, 2nd month, 3rd month and 6th month postoperation. After follow-up, pictures of the wounds will be taken, and data will be evaluated.

In addition, all of the patients will be given a schedule of intervention dates and follow-up appointments. These evaluations will be performed by an assistant who will be involved neither in the randomisation nor in the treatment.

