## Assignment of interventions: allocation

### Sequence generation

A statistician who is independent and separate from the research team will use the SAS (SAS Institute Inc, Cary, NC, USA) randomisation programme to generate random numbers with simple randomisation.

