## Statistical methods

### Statistical methods for primary and secondary outcomes

SPSS 22. 0 (IBM, Armonk, NY, USA) software will be utilised for statistical analysis. *P* ≤ 0. 05 will be considered statistically significant.

The primary outcomes will be compared between groups by using Pearson’s chi-squared test. *t*-test, corrected *t*-test (equal variance not assumed), and analysis of variance for repeated measurements will be used for data analysis, and grade data will be assessed via Wilcoxon two-sample test.

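### Covariates for the additional logistic model are chosen from the trial's own univariate results, and centre is named in no analysis

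*Protocol article*

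**What the plan says.** All references are to the Protocol article.

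- **Methods for additional analyses.** The adjusted analysis is a logistic model: "The hybrid control will use multivariate logistic regression and odds ratio and 95% confidence interval estimation". Its covariates are set by one rule: "Clinically significant variables from the univariate analysis will be included in the multivariate model". Fit is to be judged by the Hosmer–Lemeshow test. The section does not say which outcome is modelled.
- **Statistical methods for primary and secondary outcomes.** The main comparison carries no covariates: "The primary outcomes will be compared between groups by using Pearson’s chi-squared test". The *t*-test, its unequal-variance form, repeated-measures analysis of variance and the Wilcoxon test are also listed. Centre does not appear.
- **Study setting and Sequence generation.** "The study will be completed at three research centres". Allocation uses an SAS "randomisation programme to generate random numbers with simple randomisation". No blocking or stratification by centre is stated.
- **Sample size.** "We assume that no difference in efficacy exists among the three centres". This is a planning assumption. The section gives means of about 15 and 25 days, 47 per group before losses, and then: "Considering a loss to follow-up of 10%, the sample size for each group is 52 cases".

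**The concern.** Which variables enter the adjusted model is decided after their associations have been seen in the trial data. The same is true whether the phrase about clinical significance means a p-value screen or a clinician's judgement of the univariate results. The reported odds ratio then depends on which variables happened to pass, and its 95% interval is computed as if they had been fixed beforehand. Several adjusted estimates become available and nothing in the text fixes which one counts.

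Centre is the factor one would most want to name in advance. Hospitals differ in surgeons, aftercare and perhaps in how healing is judged. Simple randomisation does not balance arms within hospital, the main tests do not use centre, and the only route into a model is the univariate screen. If hospitals differ in healing time, that variation stays in the error term.

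**Working it through.** **1. The plan's own figure.** The target is 47 evaluable per group for a 10-day difference, two-sided 0.05, 80% power. No SD is stated, so 47 cannot be reproduced. It can be solved backwards. With the standard formula n = 2σ²(1.960 + 0.842)²/δ², where (1.960 + 0.842)² = 7.849:

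σ = √(47 × 100 / (2 × 7.849)) = 17.3 days.

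This SD is an assumption used below. (The formula as printed lacks the factor 2 and would imply 24.5 days; that is a separate point.)

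**2. Imbalance within centres.** Centre sizes are not given. Assume 35/35/34. Under simple 1:1 allocation, the chance of a split of 60:40 or worse is:

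- n = 35: 2 × P(X ≤ 14) = 0.311
- n = 34: 2 × P(X ≤ 13) = 0.229
- at least one of the three centres: 1 − (0.689)² × 0.771 = 0.63

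With assumed sizes of 70/20/14 it is 0.75.

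**3. What ignoring centre costs.** Assume 94 evaluable patients, three near-equal centres, within-centre SD 17.3 and centre means shifted by −d, 0, +d days. If centre is ignored, its variance 2d²/3 joins the error: SD = √(17.3² + 2d²/3). Approximate power is Φ(10/(SD × √(2/47)) − 1.960). Simulated power (8,000 trials per row) is alongside.

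| d (days) | SD ignoring centre | Power, formula | Power, simulated, ignoring centre | Power, simulated, centre in model |
|---|---|---|---|---|
| 0 | 17.3 | 80% | 79% | 78% |
| 5 | 17.8 | 78% | 76% | 78% |
| 10 | 19.1 | 72% | 70% | 78% |
| 15 | 21.2 | 63% | 61% | 78% |

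The formula uses the normal approximation and equal arms, so it runs slightly high. Simulated type I error is 5.1–5.5% with or without centre (Monte Carlo SE about 0.25 points).

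**4. What the screen does to type I error.** Simulation of 104 patients, 6 or 10 candidate covariates, entry at univariate p < 0.05 (all assumed), 4,000 trials per setting:

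- screened logistic model: 5.0–5.2%
- better of the unadjusted and screened p-values: 5.5–6.6%

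So screening alone leaves the error rate about nominal. The inflation comes from choosing between models, and it is small.

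**5. Event counts.** The Background puts healing after fistulotomy above 90%. If that carried over to total cure or recurrence, failures would be at most about 0.10 × 104 = 10.4, or 10 patients. At ten events per parameter that supports about one parameter, and ten Hosmer–Lemeshow groups would hold about one event each.

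**The case against.** The strongest reply is that this is an additional analysis, that the primary comparison is fixed elsewhere as unadjusted, and that a covariate list is usually left to the full protocol or SAP. The first two parts stand and limit the weight of the point. The third does not remove it: the article states a selection rule, and a later document that fixed the covariates would contradict it.

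Four stronger readings are tempting and are not supported.

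- **That centre has been assumed out of the analysis.** The equal-centre statement sits in the sample size section. The statistical sections neither include nor exclude centre, and it could be a candidate in the screen.
- **That chance imbalance between centres biases the comparison.** Under simple randomisation it does not do so on average. Type I error stays nominal and the loss is one of precision, present only if centres differ. No document figure shows that they do.
- **That simple randomisation undermines the sample size.** A 52/52 split occurs in only 7.8% of trials, and one arm starts below 47 in 28%, but the other arm is then larger. With SD 17.3 and 10% loss, power is 79.0% at 52/52, 78.5% at 46/58 and 77.5% at 42/62, the edge of the 95% range. The loss is about 1.5 points.
- **That the logistic model is unworkable throughout.** The sparse-event argument reaches recurrence and total cure. It does not clearly reach 14-day cure, given expected mean healing of 15 and 25 days. The 90% figure is background, not a planning rate, and the same section quotes recurrence of 0–65% across procedures.

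**Conclusion.** The point holds in a limited form. The covariate rule makes the adjusted estimate data-driven, its interval does not reflect the selection, and the most obvious covariate has no guaranteed place. This affects the credibility of the additional analysis and forgoes precision that would cost almost nothing to keep. It does not invalidate the primary comparison.

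The gain from including centre depends on how far centres differ: about 2 points of power at ±5 days, 8 at ±10 and 17 at ±15, against a loss of about 1 point if they do not differ. These figures rest on the back-solved SD, near-equal centre sizes and assumed centre shifts. The finding about the selection rule rests on the text alone.

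**What to change.** Before unblinding, delete the univariate-selection sentence and prespecify one adjusted model for wound healing time: arm, centre and a short fixed list of baseline variables already collected, for example age and BMI, all retained whatever their observed association.

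For binary outcomes expected to have few events (recurrence and total cure), limit the model to arm and centre, for example a centre-stratified Mantel–Haenszel risk difference or Firth logistic regression, and drop the Hosmer–Lemeshow test. State which outcome each model serves.

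The cost is a change of wording and two degrees of freedom for centre. Blocking within centre would be the design remedy but is probably too late: the Trial status section expected completion by 24 October 2022, before the article appeared in July 2023. If the data have already been unblinded, the fixed model can still be reported, labelled as specified after the fact.

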### Analysis methods for handling protocol nonadherence and any statistical methods for handling missing data

Study populations include the intent-to-treat analysis set defined as all randomised patients and the per-protocol analysis set defined as all patients in the intent-to-treat population without any major protocol deviations. Multiple imputations will be used to manage missing values.

### Plans to give access to the full protocol, participant-level data and statistical codes

Data, *the full protocol and statistical code* are available upon reasonable request. All inquiries about data sharing should be directed to [contact].

## Oversight and monitoring

### Composition of the coordinating centre and trial steering committee

The steering committee consists of three members, including two senior colorectal surgeons and a statistician, who will supervise the trial and ensure data safety and quality. The committee is independent of the research team and has no conflict of interest with the investigators. The committee will provide regular supervision, hold monthly meetings and organise a field trip at least once to ensure that the trial is performed smoothly and ethically. Moreover, a supervisor will ensure the authenticity and integrity of the data. During the visit, the steering committee will interview the investigators, check the original research documents and the registration of subjects and confirm whether the clinical centre complies with the research protocol. Any noncompliance with the agreement will be fully recorded by using a violation report form. Furthermore, they will identify the problems in the trial and propose suggestions for the modification of the protocol. If any decision to amend the protocol has to be made, the approval will be sent to the institutional medical ethics committee in writing, and the investigator will be notified in writing after approval. The protocol will be immediately updated in the system.

### Composition, role and reporting structure of the data monitoring committee

The data monitoring committee will include three members, namely an EDC system administrator, a data administrator and a statistician. The committee is independent of the research team and has no conflict of interest with the investigators. They will perform data management design, processing and regulation, quality control, security and confidentiality measures and EDC system management.

### Adverse event reporting and harm

#### Observation and recording

Any adverse reaction during the study period will be recorded on the adverse event form. Follow-up investigation will include detailed records of the treatment process and results and will be conducted until the laboratory examination returns to normal and the symptoms and signs disappear.

#### Medical treatment

When an adverse reaction is discovered, the investigator will decide on the diagnosis and treatment measures on the basis of the condition. They will also decide whether to terminate the observation. In the event of a serious adverse event, the unit undertaking the clinical research will immediately take necessary measures to protect the safety of the subjects.

#### Reporting of adverse events

The investigator will evaluate each adverse event, and if a serious adverse event occurs, it will be reported in accordance with the requirements of serious adverse event reporting.

All adverse events will be recorded on the adverse event page of the medical record report form. For each adverse event, the duration, severity and test drug, including the relevance and necessity to take measures as well as the taken treatments, will be described.

#### Requirements for reporting serious adverse events

If a serious adverse event occurs, the investigator will take appropriate treatment/rescue measures for the subject in accordance with his own clinical judgement to protect the safety of the subject.

The investigator should notify the main investigator and the ethics committee of the clinical research institution by the fastest means of communication within 24 h after learning of the serious adverse event. The investigator will submit the completed serious adverse event report form to the lead unit and the main investigator, who will file it with the team leader’s ethics committee within 3 days of being informed.

#### Frequency and plans for trial auditing

The trial conduct will be audited every 2 months.

#### Plans for communicating important protocol amendments to relevant parties (e.g. trial participants and ethical committees)

Committees will identify the problems in the trial and provide suggestions for the modification of the protocol. If any decision to amend the protocol is to be made, a written application will be submitted to the institutional ethics committee, and the investigator will be notified in writing after approval. The protocol will be immediately updated in the system.

#### Dissemination plans

All presentations will protect the integrity of the primary research objectives. None of the data that compromise blinding will be released before results are available. The steering committee will discuss the recommendations on the timing of these final data that may be presented at the meetings. The primary outcomes will be published in abstract books and articles.

## Discussion

Anal fistulas are common problems in the clinic. Although they have been investigated intensively by many surgeons, studies on anal fistulas remain insufficient. Some highly complex fistulas remain surgically challenging. Long postoperative wound healing times continue to be a problem for anal fistulas. Numerous techniques have been developed for anal fistula treatment. This situation shows that while colorectal surgeons have made great efforts to find a superior method for treating anal fistulas, no “gold standard” methods for this common clinical problem exist. Surgical options mainly vary depending on the preoperative classification of fistulas [12]. Eliminating all sepsis completely and permanently, achieving healing and minimising the incidence of recurrence while preserving anal function and continence are the aims of anal fistula surgery [13]. Shortening wound healing time is another important aim.

Fistulas are laid open to allow healing to start from the base [9]. Skin grafting has been shown to be an effective treatment for the rapid coverage of ulcers. Therefore, we will apply skin grafting for the wound healing of simple and low anal fistulas. Because for anal fistulotomy, the simpler the fistula, the less muscle is cut, and the more proximally the tract crosses the sphincter, the higher risk of impairing the continence. Low simple intersphincter anal fistulas are the ideal indication for skin harvesting and grafting at the surgical wound in one stage. Harvesting skin at the surgical wound avoids impairing other parts of the body and is, therefore, minimally invasive for patients. The indicators that we chose for this trial are widely used to describe and assess the efficacy and safety of anal fistula treatment. We anticipate that our results will show that the one-stage SSG of surgical wounds is effective for treating low simple intersphincter anal fistulas. Our supposition will be confirmed by this study.

## Trial status

The recruitment began on 25 March 2021, and we expect that this study will be completed by 24 October 2022.

## Data Availability

The data used to support the findings of this study will be available from the Chinese Clinical Trial Register (ChiCTR2000039174) within 6 months after the trial is completed.

## Abbreviations

SSG: Shaped skin grafting
RCT: Randomised controlled trial
GZUCM: Guangzhou University of Chinese Medicine
MRI: magnetic resonance imaging
CRF: Case report form
eCRF: Electronic case report form
EDC: Electronic data capture
